## Abstract

**Background:**

Long COVID is a multisystemic condition which affects quality of life and implies a multidisciplinary treatment approach. There is still limited evidence on management techniques for this syndrome. “Telerehabilitation” could be an important tool when addressing the symptoms of this patients with the aim of increasing their quality of life. The purpose of this trial is to analyse the effectiveness of an online multimodal rehabilitation programme to improve the symptomatology of people with long COVID and their quality of life.

**Methods:**

A pragmatic randomised controlled trial will be performed with two parallel groups: (1) usual treatment by the primary care practitioner (Treatment as usual, TAU; control group) and (2) TAU plus the use of an online multimodal rehabilitation programme, including videoconferences and content published on a Moodle platform (intervention group). The data will be collected before and after the intervention. A follow-up will take place 3 months later.

**Discussion:**

There is still a lack of knowledge regarding the management of the symptoms of long COVID. This creates the need to add scientific evidence about the care of this disease, considering that multidisciplinary social and health teams can offer the necessary care so that these patients can recover their previous quality of life.

**Clinical trial registration**: The protocol for this study was registered with the ISRCTN Registry [registration number: ISRCTN15414370] on 28 December 2022.

## Introduction

1.

In March 2020, when the coronavirus disease 2019 (COVID-19) pandemic was declared, hardly anyone would have thought that this disease would affect the physical and mental health of the entire world in the way that it did, and that it could even be considered a chronic condition (1, 2) As the pandemic has progressed, we have seen that after the initial acute infection by severe acute respiratory syndrome coronavirus 2 (SARS-CoV-2), some people develop a long-lasting multi-organ syndrome with various symptoms (general, respiratory, neurological, cardiovascular, gastrointestinal and psychosocial symptoms), a phenomenon that also occurs with many other viral disorders. The World Health Organization (WHO) called this condition “long COVID” (3–5). In the long term, these symptoms lead to a significant decline in the functional status and quality of life of people who experience them. Indeed, these symptoms limit the ability of people to perform basic activities of daily living (ADL), such as bathing or dressing, as well as occupational, social and leisure activities (6–8).

People with long COVID exhibit heterogenous symptoms and this multisystemic condition implies the need for a multidisciplinary treatment approach (9, 10). In current clinical practice, the treatment is based on managing the symptoms and the affected systems of each patient (11). In other words, a single care strategy is not possible for all people with long COVID; it is necessary to develop personalised care programmes (12).

Several guidelines about the management of long COVID have already been published (13–17). However, these clinical guidelines are not fully supported by scientific evidence, leading to a large practice gap (17). This lack of knowledge about the management and treatment of symptoms by general practitioners (GPs) has led to people with long COVID feeling that their concerns are not being taken seriously (18). Consequently, these patients have expressed their willingness to try anything (over-the-counter medications, different types of therapy, home remedies, dietary changes, supplements, etc.) to ameliorate the disabling symptoms. These types of measures can be harmful if they are not supervised by a qualified medical professional, a fact that supports the urgent need to generate evidence concerning the clinical management of long COVID (19, 20). However, this also shows that in the research carried out about long COVID, it is crucial to listen to the narratives and experiences of patients, turning them into co-producers of scientific knowledge (21).

There have been significant technological advances in recent years (22). The use of technology has been raised as an alternative to provide various rehabilitation services remotely (23). This approach increased especially during the COVID-19 confinement, when face-to-face contact between patients and health care professionals was limited, and the population was highly virtualized (24, 25). This type of care is commonly called ‘telerehabilitation’, a promising means that includes different techniques, among which are messages or phone calls, videoconferences or the use of Internet platforms (26). These types of programmes make it possible to provide, in real or deferred time, safe and supervised care at the patient’s home or other important environments (27). The advantages of telerehabilitation include greater participation and commitment on the part of the patients, a more rigorous follow-up of the intervention, personalisation of the treatment plans and, above all, a good perception on the part of those who receive it, because it favours accessibility and reduced waiting times (28).

Although more studies are needed to guarantee an adequate level of scientific evidence, telerehabilitation could represent an important element in the comprehensive rehabilitation of patients in the acute phase and with sequelae of COVID-19 (10). Aiyegbusi et al. (29) already indicated that videoconferences could be an effective tool in the follow-up of people with long COVID and that, as long as it is feasible, digital therapy programmes could be implemented through a platform that includes non-pharmacological interventions, such as respiratory rehabilitation. Moreover, Samper-Pardo et al. (30) are studying the use of mobile applications to improve the quality of life of people with long COVID, and Ozduran et al. (31) are analysing the effectiveness of YouTube videos to manage pain, a very significant symptom in this patient population.

This trial will investigate long COVID and its management by multidisciplinary social health care teams. The objective is to analyse the effectiveness of a multimodal rehabilitation programme, with online and in-person components, to ameliorate the characteristic symptoms of long COVID and, consequently, to improve quality of life. A secondary objective is to analyse the factors associated with the effectiveness of this intervention in people with long COVID.

## Methods

2.

### Research design and study registration

2.1.

This pragmatic randomized controlled trial will include two parallel groups: (1) usual treatment by the primary care practitioner (Treatment as usual, TAU; control group) and (2) TAU plus the use of an online multimodal rehabilitation programme (intervention group). The results will be reported by following a pre-established plan based on the CONSORT guidelines (32) to compare the two groups. Figure 1 shows a systematic overview of the study.

**Figure 1 fig1:**
[figure not shown]
SPIRIT schedule of enrolment, allocation, intervention and assessments.

The protocol for this study was registered with the ISRCTN Registry (registration number: ISRCTN15414370) on 28 December 2022, and is being reported using the SPIRIT (Standard Protocol Elements: Recommendations for Interventional Trials) (Supplementary materials).

### Patient inclusion and sample size

2.2.

The study population will follow the following inclusion criteria: (1) people over 18 and under 80 years of age; (2) with persistent COVID symptoms for at least 3 months since acute infection, and are not explained by an alternative diagnosis; (3) who are part of long COVID associations in Spain. The exclusion criteria will be the presence of a serious uncontrolled medical illness that may interfere with adherence to the rehabilitation programme; receiving structured rehabilitation or psychotherapeutic treatment by health care professionals; participation in another clinical trial in the last 6 months; considerable risk of suicide; pregnancy or lactation; and the presence of any medical, psychological or social problems that could seriously affect the patient’s participation in the study.

The research team will inform the presidents of the different Spanish long COVID associations about this project; they will then pass the information to the members of these organisations. Those interested in participating should contact the project researchers by using the contact details provided in the invitation letter sent to the associations. The evaluating researcher will then contact the participant and determine whether the patient can be included in the study (based on the inclusion and exclusion criteria). Recruitment and baseline assessments will be carried out until the sample size has been reached.

In accordance with the results obtained in the literature (33), to detect a mean difference of 20 points on the physical scale of the 36-Item Short Form Health Survey Questionnaire (SF-36), with a standard deviation (SD) between the groups of 36.16, an alpha value of 0.05 and a power of 80%, 53 subjects per group will need to be recruited (106 subjects in total). We will increase this value by 10% to cover potential losses in the study, so the minimum sample required will be 116 subjects. Considering a mental scale, to detect a mean difference of 20 points, with an SD of 29.99 between the groups, an alpha value of 0.05 and a power of 80%, 35 subjects per group will need to be recruited (70 subjects in total). This number will be increased by 10% to counter possible losses, so the sample size is 77 subjects. Based on these calculations, the minimum sample required for the study will be 58 subjects per group (116 subjects in total). The sample size has been calculated using the Fisterra Guide for Determination of sample size (34). The formulae used have been added as Supplementary materials.

At the time of writing 90 participants (77.5% of the target sample size) have been recruited.

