### Statistical analysis

2.7.

First, a descriptive analysis (frequencies and percentages for categorical variables; and means and standard deviation for continuous variables) and a univariate analysis [one-way analysis of variance (ANOVA) for quantitative variables and the chi-square test for qualitative variables] will be used to examine the data and to test whether there are baseline differences between the groups after randomisation. Second, to answer the main objective—whether there are differences between treatment groups regarding their effectiveness in improving quality of life, linear mixed-effects models (LMEMs) (85) will be used. Cohen’s *d* will be calculated from the estimated mean values of SF-36 and its standard deviations (SD) at baseline (86). Moreover, LMEMs with the same aforementioned components will be used to analyse whether there are differences between the groups with respect to the improvement of the secondary variables.

The results from the trial will be presented as regression coefficients for predicting change in primary and secondary outcomes with 95% confidence intervals. LMEMs will be tested against a Bonferroni-adjusted alpha level of 0.01 (0.05/5) (87).

Data collection and statistical analysis will be performed by using Excel software, R statistical software (version 3.6.2) (88) and SPSS software (version 25.0) (89).

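### The trial is sized for 80% power at alpha 0.05, but the mixed models, including the primary SF-36 model, are to be tested at 0.01, and the five tests behind 0.05/5 are not named

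*Protocol article*

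**What the plan says.** For the SF-36 physical scale, section 2.2 (Patient inclusion and sample size) assumes a 20-point difference and an SD of 36.16. The size is then derived in these terms: "an alpha value of 0.05 and a power of 80%, 53 subjects per group will need to be recruited (106 subjects in total"). For the mental scale it takes the same 20-point difference "with an SD of 29.99 between the groups, an alpha value of 0.05 and a power of 80%, 35 subjects per group". On losses it says "We will increase this value by 10% to cover potential losses in the study", and it concludes that "the minimum sample required for the study will be 58 subjects per group (116 subjects in total").

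Section 2.6.1 makes SF-36 quality of life the main variable and describes a physical and a mental summary component. It does not rank the two.

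Section 2.7 (Statistical analysis) assigns linear mixed-effects models to the main objective and models of the same form to the secondary variables. It says how results for primary and secondary outcomes will be presented, and the next sentence is "LMEMs will be tested against a Bonferroni-adjusted alpha level of 0.01 (0.05/5"). Nothing limits that level to the secondary outcomes, and nothing says which five tests the divisor counts.

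**The concern.** The two sections give different significance levels for the same primary analysis. A sample size is valid only for the level at which the test is run. If the primary SF-36 model is judged at 0.01, the 80% in section 2.2 describes another test, and the chance of detecting the planned difference is lower than a reader is told.

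There is also a problem of interpretation. A primary p-value between 0.01 and 0.05 would be significant at the level in section 2.2 and not significant at the level in section 2.7. That choice has to be settled before results are seen. Because the five tests are not named, a reader cannot tell whether the primary was meant to be in the family.

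**Working it through.** **Inputs, all from section 2.2:** difference 20 points on each scale; SD 36.16 (physical) and 29.99 (mental); alpha 0.05; power 80%; 53 per group evaluable and 58 per group recruited. The testing level of 0.01 is from section 2.7. Sidedness is not stated, so I took two-sided, because that reproduces the plan's figure.

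**Step 1: reproduce the plan's figure.** The normal approximation is n per group = 2 × SD² × (z₁₋α/₂ + z₀.₈₀)² / difference². For the physical scale this is 2 × 36.16² × (1.960 + 0.842)² / 20² = 51.3, so 52. The exact calculation with the noncentral t distribution gives 53, the stated figure. A one-sided test would give 41 to 42, which does not match. The section 2.2 calculation is therefore right for alpha 0.05.

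**Step 2: power at the level in section 2.7.** Noncentrality = difference / (SD × √(2/n)). For the physical scale with 53 per group this is 20 / (36.16 × √(2/53)) = 20 / 7.02 = 2.85. For the mental scale it is 20 / (29.99 × √(2/53)) = 20 / 5.83 = 3.43. Power from the noncentral t with 2n − 2 degrees of freedom:

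| Scale | n per group | Power at 0.05 | Power at 0.01 |
|---|---|---|---|
| Physical | 53 | 80.5% | 58.9% |
| Physical | 58 | 84.0% | 64.0% |
| Mental | 53 | 92.5% | 78.9% |
| Mental | 58 | 94.5% | 83.2% |

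The normal approximation gives 60.7% in place of 58.9% and 65.6% in place of 64.0%, so the result does not depend on the method.

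**Step 3: detectable difference.** Solving for the physical-scale difference that has 80% power with 53 per group gives 19.9 points at alpha 0.05 and 24.4 points at alpha 0.01.

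**Step 4: size needed at 0.01.** Keeping 80% power for 20 points on the physical scale needs 79 per group (77 by the normal approximation), against the 53 planned.

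**Step 5: what baseline adjustment could recover.** The article gives neither the model terms nor a correlation, so this step is an assumption. If the model adjusts for baseline as an analysis of covariance does, the effective SD is 36.16 × √(1 − ρ²), where ρ is the correlation between baseline and outcome. Physical scale, alpha 0.01:

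| Assumed ρ | Effective SD | Power, 53 per group | Power, 58 per group |
|---|---|---|---|
| 0 | 36.16 | 59% | 64% |
| 0.3 | 34.49 | 64% | 69% |
| 0.5 | 31.32 | 75% | 79% |
| 0.6 | 28.93 | 82% | 86% |

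**The case against.** The strongest objection is that 59% does not describe the planned test either. It comes from a two-sample t-test, whereas section 2.7 specifies mixed models and section 2.6 collects data before the intervention, after it and at 3 months. A reader might infer that the trial's real power is 59%. The documents do not support that. The figure is the power under the protocol's own planning model with the loss allowance used up, and step 5 shows that it could be materially higher. That part of the objection stands. It does not remove the mismatch, because section 2.2 claims no gain from baseline data and supplies no correlation from which to compute one.

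A reader might also infer that a true 20-point benefit leaves a 4 in 10 chance of a negative trial. That holds only if the physical score alone decides, which the protocol does not say. Both SF-36 components are described and both are sized for 20 points. With 53 per group at 0.01, if success on either component counted, the chance of missing both would be 0.411 × 0.211 = 9% if they were independent and 21% if fully correlated. If both had to succeed, the chance of failure would be 41% (fully correlated) to 1 − 0.589 × 0.789 = 54% (independent). The correlation is an assumption, and the success rule is not defined.

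It can also be said that the 0.01 was meant for secondary outcomes only. That may be so, but the text does not say it, and the sentence directly before concerns primary and secondary outcomes together. Finally, a stricter level does not inflate false positives or bias the estimate; its cost is power. That is correct, and it is why the remedy is one of wording.

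**Conclusion.** The point holds as an inconsistency between sections 2.2 and 2.7; no arithmetic in the 53 per group is wrong. Read as written, the primary SF-36 model is tested at 0.01, and the 80% power belongs to a test at 0.05. Under the two-sample, two-sided planning model with the protocol's SDs, the physical scale, which sets the sample size, has about 59% power for 20 points with 53 per group and 64% if nobody is lost. The mental scale loses less and stays near 80%. Baseline adjustment might bring the physical scale to between 64% and 82% with 53 per group, for assumed correlations of 0.3 to 0.6. The conflict between the two levels is certain; the exact power of the mixed model is not, because it depends on inputs that the article does not give.

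**What to change.** Before unblinding, reconcile the two levels and name the tests that make up the family of five. Then do one of the following.

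(a) State in section 2.7 that the primary SF-36 analysis is tested at an overall two-sided 0.05, and limit the 0.01 level to secondary outcomes. Add a prespecified rule for the physical and mental components at one named primary time point. A fixed sequence is one example; the sponsor should justify the order, since the protocol does not rank the two scores. If the physical score comes first at 0.05, its calculation in section 2.2 stands as written.

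(b) Keep 0.01 for the primary and restate section 2.2: about 59% power for 20 points on the physical scale with 53 per group, and a detectable difference of 24.4 points at 80% power, both labelled as two-sample figures. If the sponsor wants credit for baseline adjustment, the assumed correlation should be stated beside the figure.

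The cost is wording in two sections. No extra patients are needed under either option, which matters because section 2.2 reports 90 of the 116 already recruited. The price of (a) with a fixed sequence is that the second component cannot be claimed unless the first succeeds. The price of (b) is a less favourable stated power.

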### Randomisation, allocation and masking of the study groups

2.3.

Patients will be randomised once baseline data have been collected. Individual randomisation will be performed by an independent statistician using a computer-generated random number sequence with no restrictions. The sequence will be concealed throughout the study. Given the nature of the interventions, the patients will not be blind to their allocation. The information for the random allocation sequence will be implemented by phone by a research assistant (RA), who will state the type of treatment assigned for each new patient. The participants in the intervention group will be informed about what the intervention is and where and when they should carry it out. In addition, the RA will request that participants do not inform other researchers of their group allocation.

### Data collection and monitoring

2.4.

A RA will collect the data, and another will enter and encode the identification data. All RAs handling the data will be blind to patient allocation, as will the RA performing outcome assessment and data analysis. All the information collected will be treated in accordance with the provisions of the current legislation on the protection of personal data.

Any serious unexpected adverse event or result will be discussed by the trial management committee (the authors of this protocol). There are no plans to discontinue or modify the interventions, to improve adherence or to promote participant retention. The committee will monitor enrolment, treatment, attrition rates and any concerns related to the study. The reasons for abandonment will also be recorded.

### Intervention

2.5.

Patients assigned to the control group will follow the treatment as usual provided by their GP.

Patients assigned to the intervention group will follow the treatment as usual provided by their GP and will participate in a multidisciplinary online multimodal rehabilitation programme. The programme will be aimed at addressing the symptoms of people with long COVID and improving their quality of life. This objective will be pursued by providing exercises and therapeutic recommendations related to physical activity, respiratory rehabilitation, cognitive rehabilitation, diet, sleep hygiene, use of community resources and emotional management.

#### Intervention tools

2.5.1.

The rehabilitation will be carried out through two techniques that are typically used in telerehabilitation programmes. On the one hand, a group videoconference will be convened weekly, in which follow-up and personalisation of the contents of the intervention will be carried out. On the other hand, a Moodle (Modular Object-Oriented Dynamic Learning Environment) Platform will be used as support; it will contain all of the content provided to patients during the videoconferences.

The programme will consist of eight videoconference sessions (one per week) of approximately 1.5 h each through the Google Meet application. Three groups will be planned for each session so that patients can choose which group to attend according to their availability, and with the goal of achieving the maximum possible assistance. In addition, dividing all patients into three smaller intervention groups (a maximum of 18 people per group) will make the intervention more individualised.

The sessions will be oriented towards managing each type of symptomatology (cognitive, respiratory, physical, etc.) while addressing the different impacts on quality of life (work, social and emotional impact) and offering recommendations that can positively influence the health of this type of population (Table 1). The same content will be provided in all three groups. The sessions will not be recorded. If a person misses a session, he/she will be able to make up for it during the schedule of one of the other two groups.

**Table 1 tab1:** Content of the videoconference sessions.

Videoconference sessions	
Session 1	Management of neurological and neurocognitive symptoms Cognitive stimulation guidelines
Session 2	Management of respiratory symptoms
Session 3	Management of physical symptoms
Session 4	Diet recommendations to address long COVID symptoms
Session 5	Sleep disorders Sleep hygiene
Session 6	Emotional impact of long COVID
Session 7	Social impact of long COVID
Session 8	Compilation of therapeutic recommendations Doubts and questions

Also, a Moodle Platform will be created, where all the material and content provided throughout the telerehabilitation programme will be available. The platform will be divided into eight sections, whose name and content will coincide with each videoconference session (Table 1). For example, in the first section, patients will be able to find content related to the neurocognitive symptoms of long COVID and how to deal with them. This same subject will be discussed during the first videoconference of the programme.

Patients will be able to find the following content on the Moodle Platform:Access links to videoconferences (Google Meet application);PowerPoint presentations displayed during videoconferences;Lists of exercises and therapeutic recommendations, including cognitive exercise books, respiratory physiotherapy videos, list of diet recommendations, etc.;Forums to debate and interact on aspects addressed during the videoconference;Other resources of interest (news, glossary of terms, web pages or social networks of interest, etc.).

Instructions for how to access the weekly videoconferences and the online platform will be provided to each patient before starting the intervention, both verbally (by phone) and in writing (by email).

To carry out the rehabilitation programme, patients may use any of their personal devices: mobile phone, computer, tablet, etc., although the health team will recommend using a computer in order to avoid visual fatigue, especially when performing cognitive exercises.

In the event that any of the patients have difficulties accessing videoconferences or the platform, the rehabilitation team will try to solve them as soon as possible together with the patient.

